### 9.1.1. Sensitivity Analyses of the Primary Endpoint

The primary efficacy endpoint, mean daily weight gain (g/day), is to be assessed at Treatment Visit 9 (Day 120). Due to missing data, sensitivity analyses will be performed to assess the robustness of the primary analysis. The purpose of these analyses is to assess any potential bias due to subject assessments occurring during COVID-19 or missing data due to early dropouts or missed visits. There will be two sensitivity analyses on the

primary efficacy endpoint, mean daily weight gain (g/day) at Day 120, for both the ITT and Per-Protocol Populations.

- Exclude COVID-19 affected data: The first analysis will be to conduct the planned analysis only on the subjects who were not affected by COVID-19 at or before Day 120 (with visit window), i.e., if a subject was affected by COVID-19, then the subject will be removed from the analysis.
- Multiple imputation of missing data: The second analysis will be to conduct the planned analysis on all subjects and will use the multiple imputation method to support the analysis. The Markov Chain Monte Carlo (MCMC) method will be used to impute the missing data within each formula group under the missing at random paradigm. One hundred imputed datasets will be generated. Each dataset will be analyzed using the analysis model specified above. The final estimate of difference between formula groups and inferences will be handled using PROC MIANALYZE.

### **9.1.2. Assessment of Enrollment Time Periods**

The primary efficacy endpoint, mean daily weight gain (g/day), is to be assessed at Treatment Visit 9 (Day 120). The Brand Formula group in this analysis includes subjects that were enrolled in either phase one or phase two of the study. Due to enrollment of subjects during different time periods, we will assess the assumption that growth for subjects is similar during these different time periods. To do this we will compare the growth of subjects in the Brand Formula group that enrolled in the first phase of the study with those that enrolled in the second phase of the study. Summary statistics with 95% confidence intervals for mean daily weight gain (g/day) for all subjects in the Brand Formula group from phase one of the study and all subjects in the Brand Formula group from phase two of the study will be produced.

To assess if growth is similar between the two enrollment time periods we will generate 100 random samples from subjects in the Brand Formula group from phase one of the study. These random samples will be the same size as the number of subjects in the Brand Formula group from phase two of the study. The mean and standard error of the 100 random samples along with the 95% confidence interval for mean daily weight gain (g/day) for the Brand Formula group from phase one and the summary statistics with 95% confidence intervals for mean daily weight gain (g/day) for the Brand Formula group from phase two of the study will be summarized. This will be done for both the ITT and Per-Protocol Populations.

## 9.2. Secondary Efficacy Analysis

The following secondary endpoints (growth velocities, growth z-scores, growth measurements, and formula intake) are of interest and will be analyzed in a similar method as the primary efficacy endpoint. Each secondary endpoint will be analyzed using the Hochberg step-up multiple testing procedure to control for the familywise error rate at level  $\alpha$ . Statistical difference of formula groups will be tested using Hochberg corrected p-values. The following secondary efficacy endpoints will be analyzed:

Growth velocities:

- Mean daily length gain (mm/day) at visit 9 (Day 120)
- Mean daily head circumference gain (mm/day) at visit 9 (Day 120)

Growth Z-scores:

- Mean weight-for-age z-score at visit 9 (Day 120)
- Mean length-for-age z-score at visit 9 (Day 120)
- Mean weight-for-length z-score for age at visit 9 (Day 120)
- Mean head circumference-for-age z-score at visit 9 (Day 120)

Growth measurements:

- Mean weight (g) at visit 9 (Day 120)
- Mean length (cm) at visit 9 (Day 120)
- Mean head circumference (cm) at visit 9 (Day 120)

The average daily volume of formula intake will be compared between formula groups at visits 1, 2, 3, 5, 7, and 9.

### 9.2.1. Growth velocities

Mean daily length gain (mm/day) and mean daily head circumference gain (mm/day) over the 16-week study period and at each study visit, will be calculated as (average length or average head circumference in mm at each study visit – average length or average head circumference in mm at baseline visit)/number of days since baseline visit. The length and head circumference are measured a minimum of two times at each study visit (a third measurement is taken if the first two do not meet the threshold specified in the protocol). If two measurements are taken, then the average of the two will be used in the preceding formula. If there are more than two measurements, then the two measurements that are the closest will be averaged and used in the preceding formula. If three measurements are equidistant, then the lower two measurements will be averaged and used in the preceding formula. If there are less than 2 measurements recorded, then

the average weight measurement will be set to missing. This average measurement will be used in the calculation for mean daily length and head circumference gain above.

Descriptive statistics of the derived growth velocities (mean daily length gain and mean daily head circumference gain) will be presented by visit and formula group. A MMRM analysis will be used to compare measures between formula groups at visit 9 (Day 120). The test for statistical difference of the growth velocity between formula groups will have the following hypotheses:

H0: There is no difference in the mean daily growth velocity between the formula groups at visit 9 (Day 120).

H1: There is a difference in the mean daily growth velocity between the formula groups at visit 9 (Day 120).

Formula groups will be compared using a MMRM with sex, age at enrollment, baseline value, formula, pooled site, visit, formula by pooled site interaction, and formula by visit interaction as factors. The covariance matrix will be chosen based on the AIC criteria to choose the covariance matrix that best fits the model. 95% confidence intervals and p-values will be reported on the difference of least square means for comparison of formula groups.

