#### **14.1.1 Primary Efficacy Endpoint**

The primary efficacy endpoint, mean daily weight gain (g/d) over a 16-week study period, will be compared between formula groups by the calculation of the 95% two-sided confidence interval on the difference between the two means. Non-inferiority will be determined if the lower limit of the two-sided 95% CI for the formula difference is greater than -3, assuming a non-inferiority margin of 3 mg/d.

Infant growth will also be descriptively summarized on the basis of the following sex-specific z- scores based on World Health Organization growth charts for infants and children ages 0 to 2 years of age: weight-for age, weight-for-length, length-for-age, and head circumference-for-age z-scores. For each subject, a line listing of all raw measures of weight, length, head circumference, and all z-scores (weight-for-age z-score, length-for-age z-score, weight-for-length z-score, and head circumference-for-age z-score) will be provided. Descriptive statistics will be used to summarize weight (kg), length (cm), and head circumference (cm) and all z-score data (weight-for age, weight-for-length, length-for-age, and head circumference-for-age) by formula group for each visit. A test for non-inferiority will also be performed for length gain (cm/d) velocity and head circumference gain (cm/d) velocity.

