### 10.2.1. Anthropometric measurements

The raw anthropometric measures for weight, length, and head circumference will be collected at visits 1, 2, 3, 5, 7, and 9. These measures will be summarized by visit and formula group with descriptive statistics along with change from baseline. The weight, length, and head circumference are each to be measured a minimum of two times at each study visit (a third measurement is recorded if the first two do not meet the threshold specified in the protocol), and the average of the two or three measurements will be used

in the preceding SAS program. If there are less than 2 measurements recorded, then the average measurement will be set to missing.

Summaries of the derived anthropometric measures (weight gain (g/d) velocity, length gain (cm/d) velocity, and head circumference gain (cm/d) velocity) will be presented by visit and formula group. A MMRM analysis will be used to compare measures between formula groups at Day 120, where a non-inferiority margin,  $m$ , is 20% of the mean of the commercial brand formula. The test for non-inferiority of the anthropometric measures will have the following hypotheses:

$H_0$ : The difference in the mean anthropometric measurements between the formula groups is less than or equal to  $-m$  at Day 120.

$H_1$ : The difference in the mean anthropometric measurements between the formula groups is greater than  $-m$  at Day 120.

Formula groups will be compared using a MMRM model with gender, age, baseline value, formula, visit, site, formula by site interaction, and formula by visit interaction as factors. The covariance matrix will be chosen based on the AIC criteria to choose the covariance matrix that best fits the model. Non-inferiority will be determined if the lower limit of the two-sided 95% CI of the difference in least square means is greater than  $-m$ .

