## 6. Statistical Methods

The statistical analyses will be reported using summary tables, figures and listings (TFLs). Numbering for TFLs will be based on the recommended numbering convention provided by the International Conference on Harmonisation. Unless noted otherwise, all statistical tests will be two-sided with a significance level of  $\alpha = 0.05$ . Tests will be declared statistically significant if the calculated p-value is  $\leq 0.05$ . Continuous variables will be summarized with means, standard deviations, medians, minimums and maximums. Categorical variables will be summarized by counts and percent of subjects in corresponding categories. Missing values are not considered for percent calculations, unless stated otherwise. In those cases, footnotes will specify the percent basis. All summary tables will be presented by formula received. Select baseline tables may also include a total summary.

Individual subject data obtained via the electronic data capture (EDC) system and from external vendors will be presented in by subject listings.

The analyses described in this plan are considered *a priori*, in that they have been defined prior to the blind being broken and the database locked. Any analysis performed after breaking the blind will be considered post-hoc and exploratory. Post-hoc analyses will be labeled as such on the output and identified in the CSR.

All analyses and tabulations will be performed using SAS® version 9.4 or higher. Tables and listings will be presented in pdf and rtf format. Upon completion, all SAS programs will be validated by an independent programmer. The validation process will be used to confirm that statistically valid methods have been implemented and that all data manipulations and calculations are accurate. Checks will be made to ensure accuracy,

consistency with this plan, consistency with tables and consistency between tables and corresponding data listings.

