### **6.7. Multiple Testing Procedure**

The secondary endpoints (growth velocities, growth z-scores, growth measurements, and formula intake) will be analyzed between Brand Formula and BBN-102 w/o OPN formula groups. Each secondary endpoint will be analyzed using the Hochberg step-up multiple testing procedure to control for the familywise error rate at level  $\alpha$ . The tests of statistical difference will be tested using a Hochberg corrected p-value.

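### Protocol v5.2 promises non-inferiority tests for length and head-circumference velocity, but SAP V4 tests for a difference and sets no margin

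*Supplement*

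**What the plan says.** **Protocol v5.2.** Section 12.2 lists length-gain and head-circumference-gain velocity as secondary efficacy endpoints. Section 14.1.1 says how they are to be tested: "A test for non-inferiority will also be performed for length gain (cm/d) velocity and head circumference gain (cm/d) velocity". It gives no margin for either.

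**SAP V4 (phase two, BBN-102 against Brand).** For the same two endpoints, section 9.2.1 has as its null hypothesis "There is no difference in the mean daily growth velocity between the formula groups at visit 9 (Day 120" and as its alternative "There is a difference in the mean daily growth velocity between the formula groups at visit 9 (Day 120". No margin appears. The section plans 95% confidence intervals and p-values for the difference in least-squares means. On multiplicity, section 6.7 says "The tests of statistical difference will be tested using a Hochberg corrected p-value", and section 9.2 repeats this. Section 6.7 names the scope: "The secondary endpoints (growth velocities, growth z-scores, growth measurements, and formula intake) will be analyzed between Brand Formula and BBN-102 w/o OPN formula groups". It does not say how many tests form the Hochberg family. Section 9.2 also says the secondary endpoints are handled much like the primary one, yet the primary analysis in section 9.1 is a non-inferiority test with a 3 g/day margin.

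**Phase-one SAP (16 October 2019, BBN-001 comparison), for context only.** Section 10.2.1 did set non-inferiority hypotheses for these velocities, with a margin that "is 20% of the mean of the commercial brand formula".

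**The concern.** The study exists to show that the new formula supports age-appropriate growth. For length and head circumference the protocol frames that as a claim of non-inferiority, where the burden is on the data to exclude a deficit of a stated size. Under SAP V4 the favourable reading would come from failing to reject a null of equality, which is not evidence of similar growth.

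The Hochberg correction limits false claims of a difference. Where the difference of interest is a deficit, the correction makes that deficit harder to flag, and more so as endpoints are added.

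The two current documents therefore prescribe different hypotheses for the same endpoints. The SAP V4 document history does not mention the departure (its V1 entry is blank, and the V2 to V4 entries list other changes). Protocol section 23 requires an amendment for any change to the protocol.

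**Working it through.** **Inputs.** SAP V4 section 5 gives 104 Brand and 64 BBN-102 evaluable infants, SD 6.0 g/day, margin 3 g/day, one-sided alpha 0.025, power of approximately 90% and attrition of 25%. Section 6 gives two-sided alpha 0.05 for other tests. Section 9.2 lists 2 velocities, 4 z-scores and 3 measurements (9 growth endpoints), plus intake, which is one endpoint or six visits. The family could thus be 2 (velocities alone), 9, 10 or 15 tests. No SD, mean or power is given for length or head-circumference velocity.

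**The plan's own figure.** SE = 6.0 × √(1/104 + 1/64) = 0.953 g/day. Power = Φ(3/0.953 − 1.96) = Φ(1.187) = 88.2%, which fits approximately 90%. Enrolment also matches: 64/0.75 gives 86 and 104/0.75 gives 139.

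**Velocity endpoints in SD units.** SE = √(1/104 + 1/64) = 0.1589 SD. For a true deficit d and margin M:

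- Non-inferiority declared: Φ((M − d)/SE − 1.96).
- Difference test non-significant: Φ(z − d/SE), where z is the two-sided critical value at 0.05/k. For k above 1 this is the Hochberg worst case, in which only this endpoint is affected.

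For M I assume 0.5 SD, which is the primary margin on the SD scale (3/6.0).

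| True deficit | Non-inferiority declared (M = 0.5 SD) | Non-significant, k = 1 | k = 2 | k = 10 | k = 15 |
|---|---|---|---|---|---|
| 0.25 SD | 35% | 65% | 75% | 89% | 91% |
| 0.50 SD | 2.5% | 11.8% | 18% | 37% | 42% |

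A simulation of Hochberg with ten endpoints gave 37% at a 0.50 SD deficit when only this endpoint is affected, and 20% to 22% when all ten are.

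**How far this depends on the margin.** Setting the two formulas equal, d cancels. The difference test is the laxer one only when M < SE × (1.96 + z):

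- k = 1: 0.1589 × 3.920 = 0.62 SD
- k = 2: 0.1589 × 4.201 = 0.67 SD
- k = 10: 0.1589 × 4.767 = 0.76 SD
- k = 15: 0.1589 × 4.895 = 0.78 SD

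At M = 1.0 SD a 0.5 SD deficit passes non-inferiority Φ(0.5/0.1589 − 1.96) = 88% of the time, against 37% non-significant at k = 10.

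A margin of 20% of the Brand mean equals 0.20/CV in SD units. Non-inferiority is then the stricter test only if the CV exceeds 0.20/0.62 = 32% (against the unadjusted test) or 0.20/0.76 = 26% (against k = 10).

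**Cost of Hochberg alone.** An unadjusted test has 80% power for (1.960 + 0.842) × 0.1589 = 0.445 SD. If only that endpoint is affected, power falls to 71% (k = 2), 51% (k = 9) or 45% (k = 15).

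**The case against.** A reader might infer that, because of this switch, a real growth deficit is more likely to go unnoticed. The documents do not support that as a general statement. The comparison needs a margin, and neither current document supplies one. Under the phase-one margin of 20% of the Brand mean, a CV of 25% or less makes non-inferiority the easier hurdle, so a moderate deficit would pass more often than under the present test. The loss from Hochberg is also a worst case. Length velocity, length-for-age z-score and attained length all rest on the same Day 120 length, so a deficit would rarely touch one endpoint alone, and a family confined to the two velocities costs far less. This objection stands, and it limits what can be said about size.

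A reader might also infer that the SAP will report non-significance as comparable growth, or that it makes a non-inferiority reading impossible. SAP V4 says neither. The planned 95% confidence interval already contains the statistic that a non-inferiority decision needs, and only the margin and the rule are missing. This too stands.

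Finally, these are secondary endpoints, and the protocol's own commitment cannot be carried out as written because it has no margin. That is a reason to complete both texts. It does not justify leaving them in conflict.

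**Conclusion.** The contradiction is real and lies between the latest protocol and the latest SAP. The non-inferiority tests promised for length and head-circumference velocity are absent from SAP V4, and the tests that replace them cannot establish non-inferiority when they fail to reject.

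The size is conditional. With 104 and 64 infants and an assumed margin of 0.5 SD, a deficit equal to the margin would be cleared 2.5% of the time by non-inferiority, against 12% non-significant unadjusted and 18% to 42% under Hochberg (k = 2 to 15, only this endpoint affected). Above a margin of about 0.62 SD (unadjusted) to 0.78 SD (k = 15) the order reverses. Without a margin and CV it cannot be said which test would miss more deficits here.

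The primary weight-gain analysis keeps its non-inferiority hypothesis and margin and is untouched. The point should be fixed, but it does not threaten the main conclusion.

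**What to change.** Before unblinding:

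1. In SAP V4 section 9.2.1, replace the hypotheses for both velocities with non-inferiority hypotheses (BBN-102 minus Brand greater than −m), judged by the lower limit of the two-sided 95% confidence interval already planned.
2. Prespecify and justify m for each endpoint, in the SAP's mm/day units, and add it to protocol section 14.1.1. The phase-one 20% rule is a precedent that itself needs justification. It is not yet a number: the Brand mean comes from data that SAP V4 section 5 keeps blinded through phase-two enrolment, and no reference velocity is given.
3. In section 6.7, list the endpoints that form the Hochberg family, count intake as one test or six, and say whether the two non-inferiority claims carry any adjustment.
4. State that a non-significant difference in the other growth endpoints is not evidence of comparable growth.

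If the sponsor prefers the difference test, the protocol must be amended to say so, and statement 4 should then cover the velocities as well.

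The cost is SAP and protocol text, a table entry and the work of justifying two margins. No new data or infants are needed.

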### **9.2.2. Growth Z-scores**

Infant growth will also be descriptively summarized using z-scores based on the 2009 CDC growth charts for infants and children 0 to 2 years of age, which are based on the World Health Organization growth reference study. The following z-scores will be calculated using the average measurements: weight-for age, length-for-age, weight-for-length, and head circumference-for-age z-scores. For each subject, a line listing of all z-scores (weight-for-age z-score, length-for-age z-score, weight-for-length z-score, head circumference-for-age, and BMI-for-age z-score) will be provided. Descriptive statistics will be used to summarize the z-score data by visit and formula group. A SAS program and data to be used for the z-scores is found at

<https://www.cdc.gov/nccdphp/dnpao/growthcharts/resources/sas-who.htm>.

A MMRM analysis will be used to compare measures between formula groups at visit 9 (Day 120). The test for statistical difference of the Z-scores between formula groups will have the following hypotheses:

H0: There is no difference in mean z-scores between the formula groups at visit 9 (Day 120).

H1: There is a difference in mean z-scores between the formula groups at visit 9 (Day 120).

Formula groups will be compared using a MMRM with sex, age at enrollment, baseline value, formula, pooled site, visit, formula by pooled site interaction, and formula by visit interaction as factors. The covariance matrix will be chosen based on the AIC criteria to choose the covariance matrix that best fits the model. 95% confidence intervals and p-values will be reported on the difference of least square means for comparison of formula groups.

The z-scores generated based on World Health Organization growth reference standards will be plotted for each subject over time.

### **9.2.3. Growth measurements**

The growth measurements for weight, length, and head circumference will be collected at visits 1, 2, 3, 5, 7, and 9. The weight, length, and head circumference are each to be measured a minimum of two times at each study visit (a third measurement is taken if the first two do not meet the threshold specified in the protocol). If two measurements are taken, then the average of the two will be used. If there are more than two measurements, then the two measurements that are the closest will be. If three measurements are equidistant, then the lower two measurements will be averaged. If there are less than 2 measurements recorded, then the average weight measurement will be set to missing.

Descriptive statistics of the average growth measurements (weight, length, and head circumference) will be presented by visit and formula group. A MMRM analysis will be used to compare measures between formula groups at visit 9 (Day 120). The test for statistical difference of the growth measurements between formula groups will have the following hypotheses:

H0: There is no difference in the mean growth measurement between the formula groups at visit 9 (Day 120).

H1: There is a difference in the mean growth measurement between the formula groups at visit 9 (Day 120).

Formula groups will be compared using a MMRM with sex, age at enrollment, baseline value, formula, pooled site, visit, formula by pooled site interaction, and formula by visit interaction as factors. The covariance matrix will be chosen based on the AIC criteria to

choose the covariance matrix that best fits the model. 95% confidence intervals and p-values will be reported on the difference of least square means for comparison of formula groups.

Growth measures will be plotted for each subject over time.

